## **2.5 Sample size**

To assess the cumulative incidence after 10 months of follow-up in residential care centers in Belgium a sample of 381 participants (residents & staff) is required to estimate a proportion of 0.5 with a half-width of 5%, using a 95% Wilson score CI. As residents/staff are clustered within care facilities, the sample size will be augmented by the design effect. Assuming, 15 participants (7 residents and 8 staff) per institution after 10 months of follow-up, and an ICC of 0.12, the design effect is  $2.68 = (1 + 0.12 \times (15 - 1))$ . The total sample size required is  $1022 = 381 \times 2.68$ . At least 69 institutions, each including 15 participants, need to be included in this study, which brings the total sample size to 1035 after 10 months follow-up. In order to obtain at least 15 participants, in 69 institutions after 10 months of follow-up, assuming a drop-out rate of 0.2 and 0.4 for staff (changes in staff, sick leave and holidays) and residents (deceased, hospitalized or transferred residents), would require 22 sero-negative participants per care facility, (10 staff, 12 residents) in all 69 institutions. Assuming a seroprevalence rate of 0.5 at the baseline moment of the study would require 44 participants per care facility, (20 staff, 24 residents) in all 69 institutions.

A final sample size calculation will be performed to check whether the sample size obtained for the second research question will be sufficient for the analysis of the first research question.

To assess the seroprevalence in residential care centers in Belgium a sample of 381 participants (residents & staff) is required to estimate a seroprevalence of 0.5 with a half-width of 5%, using a 95% Wilson score CI.

As residents/staff are clustered within care facilities, the sample size will be augmented by the design effect. Based on the previous calculation, 44 participants (24 residents and 20 staff) will be sampled per institution. Assuming an ICC of 0.12, the design effect is  $6.16 = (1 + 0.12 \times (44 - 1))$ . The total sample size required is  $2347 = 381 \times 6.16$ . At least 54 institutions, each including 44 participants, need to be included in this study, which brings the total sample size to 2376 participants.

Therefore, to assess both the first (seroprevalence) and second (cumulative sero-incidence) research question, the sample size will include 69 NHs, each including 44 participants (20 staff, 24 residents). This brings the total sample size up to 3036 participants.

## **2.6 Sampling procedure**

*Stratified random sampling of nursing homes.*

A stratified random sample of 69 nursing homes from NHs in Belgium will be selected. NH-related features that will be necessary for this method of sampling will be extracted from the existing Sciensano database. The RIZIV number will be necessary to identify the selected nursing homes. The nursing homes will be equally spread over Belgium and randomly sampled within the strata defined by region and province, and in proportion to the population. Random samples from the stratified province will be taken in proportional to the number of beds. The selected NHs will be contacted for agreement to participate in this study by Ghent University.

If a NH refuses to participate, a substitute NH with a comparable profile according to the strata will be contacted. The reason of refusal will be documented to assess possible selection bias.

### *Stratified random sampling of participants*

Nursing homes that have agreed to participate will be asked to make an alphabetic list of the current staff/residents separately (service flat residents and temporary staff excluded) and to send the number of residents and staff to the Ghent University. Staff/residents will be sampled in a 5:6 ratio in each nursing home. Online statistical computing web programming will be used to generate the random sampling schedule out of the staff and resident numbers. The list of randomly selected numbers, including a list with substitute numbers, will be sent back to the NH. The NH's have to sample 20 staff and 24 residents out of their alphabetic list according to delivered random generated numbers.

When a participant refuses (after asking for oral consent) to join the study the subject according to the first following numeric list will be asked to participate. The participants will be assigned to a unique identification code of the following format: CX(X)SXXY or CX(X)RXXY for staff and residents respectively (C, nursing home (centre); S, staff; R, resident). In this way, test results and medical data are pseudonymized for the involved researchers. The link between the identification code and personal data will be safeguarded by the principal investigator. The oral consenting will be confirmed by a means of a signature before or on the day of the first data collection.

## **2.7 Data Collection**

### **2.7.1 Collection of capillary blood samples and point-of-care test procedures**

The capillary blood samples will be obtained using a lancet to finger prick the middle finger and collect a 1-10 drops of capillary blood. A capillary blood drop will be transferred to the

specimen well of a point-of-care (POC) test (COVID-19 IgG/IgM Rapid Test Cassette, Orient Gene Biotech Co.) using a plastic dropper (delivered with COVID-19 IgG/IgM Rapid Test kit). Two drops (ca. 80 µl) of Orient Gene Biotech sample buffer will be immediately added to the buffer well, with avoidance of air bubbles. If the red colour does not move across the test window or if blood is still present in the specimen well after two minutes, one additional drop of sample buffer should be added into the buffer well. The result should be read in 10 minutes, positive test results may be visible as soon as 2 minutes. The result cannot be interpreted after 15 minutes.

The results of the COVID-19 IgG/IgM Rapid Test Cassette should be interpreted as following:

- **Negative:** The coloured line in the control region (C) changes from blue to red. No line appears in the test line region M or G.
- **Anti-COVID-19 IgM positive:** The coloured line in the control region (C) changes from blue to red and a line appears in the test line M.
- **Anti-COVID-19 IgG positive:** The coloured line in the control region (C) changes from blue to red and a line appears in the test line G.
- **Anti-COVID-19 IgG and IgM positive:** The coloured line in the control region (C) changes from blue to red and a line appears in the test line G and M.
- **Invalid test:** Control line is still completely or partially blue and fails to completely change from blue to red. Insufficient specimen sample or incorrect procedural techniques are the most likely reasons for control line failure. The test should be repeated using a new cassette.

For the study any positive result of IgM or IgG will be considered as a positive result. In case of an invalid test, the test is repeated. When it is still invalid it will be noted as such. Additionally, a few drops of capillary blood will be collected on Dried Blood Spot (DBS) collection cards for (semi-)quantitative analysis of vaccine-induced/infection-induced anti-SARS-CoV-2- specific antibodies as a part of the sub-study performed by Ghent University (details are provided in appendix 6.4).

### **2.7.2 Demographic and medical data.**

Data to be extracted from the Sciensano database are a list of all nursing homes in Belgium with their RIZIV number, postal code, the capacity of each nursing home (number of beds), and suspected (CT and symptoms) and confirmed (PCR and AG POC test) COVID-19 related death rate.

At the NH level, the management will be asked, at baseline, about the proportion of care grade (according to the Katz evaluation scale) among their residents, if a COVID-19 vaccination campaign was organized in the NH yet (date, type of vaccine and vaccination coverage), the suspected and confirmed COVID-19 infection rate, the COVID-19 related and non-COVID-19 related death rate from the beginning of the crisis until now and if and when they had an outbreak (more than one COVID-19 infection that are suspected to be related). With every follow-up sampling timepoint, the NH will be asked about a vaccination campaign (when this did not take place yet at baseline), if COVID-19 testing was performed in their NH, the respective proportion of positive tests and COVID-19 related death rate.

Individual medical data, comprising medical history and if participants have experienced an episode of COVID-19 symptoms or underwent a COVID-19 (PCR/antigen) test (with mention of date and result) or if COVID-19 was confirmed by a CT-scan, reason of missing data of drop outs (death, hospitalisation, sick leave, leaving the job), and whether they received a COVID-19 vaccination (date, type of vaccine, number of doses) in both NH residents and staff will be collected through an online questionnaire at both baseline and follow-up sampling timepoints (LimeSurvey) (See Appendix 6.3 for questionnaires). The CRC will fill out the questionnaire concerning the resident participants during the week of the sampling timepoint. Therefore the head of the nursing staff or the representative of the resident can be asked to provide the data. In this questionnaire, the surveyed medical data will be linked to the participant identification code. Concerning the medical history, the participants (NH staff and residents) will be asked

for COVID-19 relevant preconditions: cardiovascular diseases, diabetes, hypertension, serious heart, lung or renal diseases, immunosuppressing conditions or medication and any form of active cancer. Furthermore, participants (staff and residents) will be asked if they received a COVID-19 vaccination (date, type of vaccine, number of doses), underwent a PCR-/ antigen-test, the date of this test and the result (if more than one test was performed, the date of the first positive test has to be given) or if COVID-19 was confirmed by a CT-scan, and, if they experienced COVID-19 symptoms and when (date). The COVID-19 symptoms episode will be defined according to the Sciensano case definition:

- At least one of following acute principal symptoms not explained by another clear cause: coughing, dyspnoea, chest pain, sudden loss of olfactory sense and/or taste;

OR

- At least two of following symptoms not explained by another clear cause: fever, myalgia, tiredness, rhinitis symptoms, sore throat, head ache, anorexia, diarrhoea, acute confusion, sudden collapse

OR

- Worsening of chronic respiratory symptoms (COPD, asthma, chronic cough) not explained by another clear cause

Additionally, staff members are asked questions concerning vaccine hesitancy (if and why they hesitated to get vaccinated against COVID-19), see Appendix 6.3.

### **2.7.3 Data collection: organisation**

Before start of the study, each study center will be assigned to a selection of NHs that agreed to participate (recruited by Ghent University). Bimonthly, rapid SARS-CoV-2 antibody-testing by means of a point-of-care (POC) test and DBS collection as part of the sub-study conducted by Ghent University (see appendix 6.4) will be organized in each participating NH. The study centers organize the SARS-CoV-2 antibody testing and the data collection in their specifically

assigned NHs. A standard operational procedure (SOP) will be developed to ensure that each study center performs the antibody testing and the data collection in the same standardized way. Additionally, the person(s) from the study centers that will conduct the antibody testing and the data collection in the NH will receive a brief training organized by Ghent University on how to conduct these tasks (this is possible in an online training). Additionally, in each NH, a contact person (local NH staff) will be assigned for communication between the study centers and NHs for study-related inquiries. The interpreted test result of the POC test will be documented by the researchers/CRC with mention of the participant identification code and collection date. If a test was not performed, the reason will be documented (e.g. hospitalisation, sick leave,...). Concerning the reporting of the results of the POC test to individual NH staff members, the test result will be interpreted by the CRC and communicated directly to the individual staff member participant accompanied by a written explanation form about the clinical meaning of the result. Concerning the NH residents, the CRC will communicate the result directly, write it down on a written form explaining the clinical meaning of the result. One copy of this form will be left by the resident, the other copy is meant for the head of the nursing staff, and can be send/forwarded to the Coordinating and advising physician (CRA) , the family or legal representative of the resident and the general practitioner of the resident.

When test results are missing, for instance when a staff member was absent on the sampling day, the study center contacts the NH in order to obtain the test result within 2 days after the sampling day for that NH. At Ghent University, the individual medical data from all participants will be extracted from the LimeSurvey database for statistical analysis. The test results and the questionnaires will both be linked to the unique participant identification number.

### **3. Data Analysis**

#### **3.1 Expected outcome**

The benefits to get out of the achievement of this study would be the following\*:

- Assessment of seroprevalence at baseline and follow-up in the cohort at month 2, 4, 6, 8, 10 and follow-up of sero-incidence over 5 two month time periods among nursing home staff and residents in NH's in Belgium.

\* For every participant, it will be registered whether a COVID-19 vaccine was administered to differentiate between vaccinated and non-vaccinated participants.

#### **3.2 Statistical analysis**

##### **Primary objectives**

1. To assess the seroprevalence of SARS-CoV-2 among NH residents and staff in Belgium at month 0 and at every follow-up visit in the cohort at month 2, 4, 6, 8 and 10.

The seroprevalence of SARS-CoV-2 among NH residents and staff in Belgium at month 0, and follow-up in the cohort at month 2, month 4, month 6, month 8 and month 10, will be reported stratified for staff and residents, as well as a total seroprevalence with the 95% confidence interval (CI), assessed by a generalized equation estimation (GEE) analysis with independence covariance structure. The average seroprevalence in Belgian NH will be estimated via a generalized equation estimation (GEE) analysis with exchangeable covariance structure. All characteristics will also be displayed for the Belgian regions separately.

2. To assess the sero-incidence of SARS-CoV-2 among NH residents and staff in Belgium over five two month time frames and summarised over a ten month time period.

The sero-incidence of SARS-CoV-2 among NH residents and staff in Belgium over 5 two month time periods, as well as summarized over a period of 10 months, will be estimated as a total sero-incidence, as well as for NH residents staff separately, via a clustered Poisson (or binomial) regression, taking the clustered nature of participants within nursing homes into account.

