## 2.4 Study design and population

We plan to perform a longitudinal cohort study with a 2-month interval serial sampling of 3036, NH residents (1656) and staff (1380), spread over 69 nursing homes throughout Belgium. Sample collection at baseline (day 0, month 0) will start in a staggered way, so all samples among the different nursing homes are collected within the first  $\pm$  four weeks after collection of the first sample. Follow-up sample collection will occur with a 2-month interval in month 2, month 4, month 6, month 8, month 10 after the baseline collection of that specific nursing home. Ideally, in each NH, the 2nd, 3rd, 4th, 5th and 6th sample collection will take place d 60, 120, 180, 240 and 300 days after the first NH sample collection. However, when collection after 60 days is not possible for practical reasons, samples should be collected within a margin of  $\pm$  7 days.

The recruited NHs will be equally spread across the Belgian territory according to geographic and demographic characteristics to guarantee general representativity. Forty-four participants (20 staff, 24 residents) will be randomly included per nursing home.

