### **Secondary objectives**

4. To assess the seroprevalence according to vaccination status among NH residents and staff in Belgium at month 0 and at every follow-up visit in the cohort at month 2, 4, 6, 8 and 10.

The seroprevalence among NH residents and staff in Belgium at month 0, and follow-up in the cohort at month 2 (and if relevant at month 4, 6, 8, and 10), will be reported according to the vaccination status (Number of shots: 0, 1 or 2) and for the subgroups ‘with’ and ‘without’ a history of self-reported SARS-CoV-2 infection, averaged over NHs based on a GEE analysis with exchangeable covariance structure.

5. To assess the risk of getting a SARS-CoV-2 infection since vaccination between:
  - Residents and staff
  - Seropositive and seronegative participants at all timepoints
  - Individuals with or without previous self-reported SARS-CoV-2 infections
  - Adjusted for the updated vaccination degree of NH at all timepoints

For vaccinated participants only, a survival analysis will be performed to investigate the time (in days) to a SARS-CoV-2 infection since vaccination between sero-positive and -negative

participants at all time points. A participant is considered to have an event when the participant had a positive PCR test result (or a positive antigen rapid test, or a positive CT scan, or a positive saliva test in absence of a PCR test). The survival or censoring time (in days) is registered since 14 days after being fully vaccinated (full dose regimen) until first event (or censoring moment). If the proportional hazard assumption holds, a stratified (by NH) Cox proportional hazards regression model will be used to model the hazard of SARS-CoV-2 infection between sero-positive and -negative participants at all time points (modelled by the inclusion of a time-varying seropositivity status), adjusted for type of participant, history of self-reported SARS-COV-2 infections, and a time-varying NH vaccination degree. The analysis will be performed stratified by type of participant or other variables, if the proportional hazard assumption does not hold.

6. To assess the proportion of confirmed COVID-19 deaths and non-COVID-19 related deaths since vaccination and the time until death (within the study timeframe) between sero-positive and -negative participants for NH residents

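### With a fixed 20 staff and 24 residents per home, the independence and exchangeable GEEs of primary objective 1 cannot separate person-level seroprevalence from the average over homes

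*Protocol*

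**What the plan says.** Protocol section 3.2, primary objective 1, sets out two analyses. Seroprevalence for residents, for staff and in total is to be "assessed by a generalized equation estimation (GEE) analysis with independence covariance structure". The next sentence reads: "The average seroprevalence in Belgian NH will be estimated via a generalized equation estimation (GEE) analysis with exchangeable covariance structure". The first item under the secondary objectives in 3.2 shows what the exchangeable structure is meant to deliver, since results there are "averaged over NHs based on a GEE analysis with exchangeable covariance structure". No weights are mentioned in either place.

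The sampling text fixes the take per home. Section 2.4: "Forty-four participants (20 staff, 24 residents) will be randomly included per nursing home". Section 2.6: "Staff/residents will be sampled in a 5:6 ratio in each nursing home", and "The NH's have to sample 20 staff and 24 residents out of their alphabetic list". On the choice of homes, section 2.6 stratifies by region and province, refers to proportionality to the population, and adds: "Random samples from the stratified province will be taken in proportional to the number of beds". That sentence can mean that each home's chance of selection is proportional to its beds, or that beds only set how many homes each province supplies.

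**The concern.** Two different quantities are of interest. One is the share of residents and staff who are seropositive, in which a large home counts for more. The other is the seroprevalence of the average home, in which every home counts once. The plan relies on the working correlation to move from the first to the second. That can work when sampled cluster sizes follow home sizes. Here they do not, because a home with many beds and one with few both contribute 44 people.

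If the two analyses return one number under two labels, readers will take it as evidence that person-level and home-level seroprevalence agree, when the data were never asked. If prevalence does vary with home size, one label is wrong. The cluster-robust interval would not reveal this, because it is built around the same estimate. The overall total raises a related question: its mix of staff and residents is set by quota, yet it is presented as describing Belgian nursing homes.

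**Working it through.** **Inputs from the protocol.** 69 homes, each with 20 staff and 24 residents (2.4, 2.5, 2.6); ICC 0.12, planning proportion 0.5, half-width 5 points, drop-out 0.2 for staff and 0.4 for residents (2.5); pilot seroprevalence 24.5% in residents and 19.1% in staff (section 1). **Assumed, not in the documents:** the spread of home sizes, the relation of prevalence to size, and the real staff share.

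**1. The plan's own figures.** The 95% Wilson half-width at p = 0.5 first falls to 5 points at n = 381 (0.04995). Design effect 1 + 0.12 × 43 = 6.16. 381 × 6.16 = 2346.96, so 2347; 2347/44 rounds up to 54 homes, or 2376 people. The final size is 69 × 44 = 3036. All reproduce.

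**2. Baseline.** An intercept-only exchangeable GEE solves Σ wᵢ(ȳᵢ − μ) = 0 with wᵢ = nᵢ/(1 + ρ(nᵢ − 1)). The independence GEE has wᵢ = nᵢ. With nᵢ = 44 everywhere both weights are constant (44/6.16 = 7.14 at ρ = 0.12), so both estimates equal the plain mean of the home proportions. The same holds for staff alone (20 per home) and residents alone (24 per home). In simulated data with 69 homes the two fits agreed to 7 decimals (for example 0.2704216 under both), with equal robust standard errors.

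**3. Follow-up.** Expected numbers per home after drop-out are 20 × 0.8 + 24 × 0.6 = 30.4. At ρ = 0.12 the exchangeable weight is 6.38 for n = 24, 6.70 for n = 30 and 7.14 for n = 44, so it varies little and depends on how many were tested, not on beds. In single simulated draws with drop-out or missing tests, totals differed by 0.02 to 0.45 points, and staff or resident estimates by up to 0.7.

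**4. What the single number estimates.** If home selection is proportional to beds, a resident's inclusion probability is proportional to beds × 24/residents, which is roughly constant. The unweighted estimate then targets residents at person level, and the home average over-represents large homes. If selection is equal within province, the unweighted estimate targets the home average within province, and the person-level figure under-represents large homes.

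Illustration with an assumed frame in which prevalence rises by 20 points per 100 beds (person-level 0.289, average home 0.245): both GEEs gave 0.276 in the draw proportional to beds and both gave 0.232 in the equal-probability draw. These are single draws with sampling error. The result followed the sampling scheme, and the working correlation changed nothing.

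**5. Possible size of the gap.** Person-level minus home-average prevalence = r × CV(size) × SD between homes, with SD = √(ICC × p(1 − p)).

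- p = 0.22: SD = √(0.12 × 0.22 × 0.78) = 14.35 points. r = 0.1, CV = 0.3 gives 0.43; r = 0.5, CV = 0.5 gives 3.59. Simulation gave 0.4 to 3.3.
- p = 0.5: SD = √(0.12 × 0.25) = 17.32 points. The same settings give 0.52 and 4.33. Simulation gave 0.5 to 4.1.
- r = 0: the gap is 0.

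**6. The total.** Quota: (20 × 19.1 + 24 × 24.5)/44 = 22.05%. Staff share 30%: 0.3 × 19.1 + 0.7 × 24.5 = 22.88%, or +0.83. Staff share 70%: 0.7 × 19.1 + 0.3 × 24.5 = 20.72%, or −1.33. Subtracting the one-decimal percentages gives +0.9 and −1.3.

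**The case against.** A reader might infer that the two figures cannot both be right, or that one is biased however section 2.6 is read. The documents do not support that. It requires seroprevalence to be related to home size, and the protocol reports no such relation. The pilot results in section 1 show wide spread between nine homes (0.0% to 38.4% in residents) but nothing about their size. With no relation, the two quantities coincide and one number is correct for both. The gaps in step 5 follow from their assumptions: a steeper assumed relation with more variable home sizes gives up to 8.5 points, and no relation gives 0. They show what is possible, not what is present.

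Three further objections have weight.

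- The average over homes is not listed as an objective in section 2.1; it is one sentence in 3.2. If homes are drawn proportional to beds, the resident figure is already roughly self-weighting and only that added figure is exposed.
- Weight construction is often left to a SAP, and one not shown might supply it. This does not answer the point, because 3.2 states a method for separating two quantities and that method cannot do so at a fixed take.
- Exact identity needs 44 valid results in every home. Invalid or missing tests will break it, but the resulting difference reflects who was tested and not home size.

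On the total, residents and staff are also reported separately, so the quota cannot distort those figures, and the shift is small beside the planned half-width of 5 points.

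**Conclusion.** The point stands in a limited form. At baseline the two GEE analyses of primary objective 1 are the same analysis for total, staff and residents, given complete quotas. At follow-up they are nearly so, and the small difference comes from attrition. That part needs no assumption beyond the protocol's own sampling numbers.

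Whether a reported figure then misses its target is conditional. It does so only if seroprevalence varies with home size and no weights are applied. The exposed figure is the home average if homes are drawn with probability proportional to beds, and the person-level figure if they are drawn with equal probability within province. The size is 0 with no relation and about 0.4 to 4 points under the assumed CVs and correlations, which is illustrative only. The quota effect on the total needs no link with home size; it is about +0.8 to −1.3 points at the pilot prevalences for assumed staff shares of 30% to 70%. The plan should be changed because a primary analysis cannot do its stated job and the repair is cheap. Bias has not been shown.

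**What to change.** In 2.6, state whether the number of beds sets each home's selection probability or only the allocation of homes to provinces. The weights cannot be computed until this is settled.

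In 3.2, define each target by its weights and not by the working correlation, keeping the home-clustered robust variance:

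- Resident, staff and total seroprevalence: weight each participant by 1/(home selection probability × within-home sampling fraction of residents or staff). The total then follows the real staff-to-resident mix.
- Average over homes: weight each home by 1/(its selection probability).
- Report the unweighted estimates as a sensitivity analysis.

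No new data are needed. Bed numbers come from the Sciensano database (2.7.2), and homes already send their resident and staff counts to Ghent University (2.6). The cost is some precision: if weights vary as home size does, with an assumed CV of 0.3 to 0.5, variance rises by a factor of about 1 + CV², that is 1.09 to 1.25, or roughly 9% to 25%. The weights will be approximate where a refusing home was replaced by a substitute, and the report should say so.

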| Secondary objectives                              | This study was designed late 2020, when COVID-19 vaccines were still in research development. However, on January 5 th , 2021, the vaccination campaign in Belgian NH started. The implementation of vaccines directly impacts the seroprevalence, meaning that some of the secondary objectives were no longer accurate (e.g., assessment of risk factors for infection). Therefore, adjustments were made to the secondary objectives, and tertiary objectives concerning the proportion in the sample that is not vaccinated were added. | 2.1 Objectives
3. Data analysis                                                                |
| Additional questions concerning vaccine hesitancy | In the first test round we observed that 15% of staff in the sample were not vaccinated against COVID-19. Therefore, we aim to explore the reason behind vaccine hesitancy by adding additional questions in the follow-up questionnaire of the following sampling point concerning if and why they hesitated/are hesitating to get vaccinated as a part of the follow-up questionnaire (one-off).                                                                                                                                                     | 2.7.2 Demographic and medical data
6.3 Appendix: questionnaires                                |
| Statistical analysis                              | The statistical analysis plan was adjusted to the changes made in the secondary objectives and addition of tertiary objectives.                                                                                                                                                                                                                                                                                                                                                                                                                        | 3. Data analysis                                                                                  |

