#### **6.4.4. Data collection and analysis**

Only biological specimens will be collected. No additional questionnaire will be needed. The collected dry blood spots will be send back to Ghent University and saved in a study-specific biobank. The collected samples will be analyzed using an Enzyme-Linked Immuno Sorbent Assay (ELISA) for (semi)-quantitative detection of anti-SARS-CoV-2 specific antibodies (anti-S1/anti-NCP). The Dry Blood Spot samples will be pseudonymized.

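### Primary objective 2 has no rule for vaccination, so one sero-incidence figure pools vaccine-induced with infection-induced seroconversion

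*Protocol*

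**What the plan says.** Primary objective 2 in section 3.2 promises an estimate of "The sero-incidence of SARS-CoV-2 among NH residents and staff in Belgium over 5 two month time periods, as well as summarized over a period" (ten months). It is to be given overall and for residents and staff, from a Poisson or binomial regression that allows for clustering in homes. Neither this text nor section 2.1 defines the event or mentions vaccination.

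The only positivity rule is in section 2.7.1: "For the study any positive result of IgM or IgG will be considered as a positive result".

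The table of changes dates the start of the nursing-home vaccination campaign to 5 January 2021 and accepts that vaccination directly affects seroprevalence. It revises the secondary objectives, adds tertiary ones and adjusts the analysis to match. It also reports: "In the first test round we observed that 15% of staff in the sample were not vaccinated against COVID-19". Table 1 in section 2.2 places the first blood collection in February 2021.

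Section 2.5 is not among the sections listed as changed. It sizes the study for 10-month cumulative incidence ("To assess the cumulative incidence after 10 months of follow-up in residential care centers in Belgium a sample of 381 participants") and gets from 22 seronegatives per home to 44 participants as follows: "Assuming a seroprevalence rate of 0.5 at the baseline moment of the study would require 44 participants per care facility".

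**The concern.** A participant who is negative at one visit and positive at the next may have been infected or may have responded to a vaccine. If both count as the same event, the figure labelled SARS-CoV-2 sero-incidence cannot be read as infection incidence. Section 4.4 sends results to public health authorities after every testing point, where that reading is likely.

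The second question is precision. The at-risk set for this objective is the baseline seronegatives, and their planned number rests on a share chosen before the campaign began.

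**Working it through.** **1. Does any part of the protocol separate the two kinds of conversion for objective 2?**

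- Section 2.7.1: positivity is any IgM or IgG, whatever the vaccination status.
- Section 3.2, objective 7: two successive negatives are taken to mean no seroconversion after vaccination. A positive rapid test is therefore the expected vaccine response.
- Section 4.5 speaks of vaccine-related sero-incidence, so the protocol recognises the distinction.
- Section 3.1, footnote: vaccination is registered for each participant so that vaccinated and unvaccinated can be told apart. No rule for objective 2 follows.
- Section 3.2, objectives 4 to 10: vaccination status is used as a stratum (4), to define the vaccinated population or the time origin (5 to 7), as the comparison (8 and 9) or to restrict to the unvaccinated (10). None of these concerns sero-incidence.
- Overall infection incidence is not given elsewhere either. Objective 5 models reported infection in vaccinated participants only. Objective 8 compares hazards, and only if there are enough unvaccinated participants.

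The answer is no.

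**2. How far could pooling move the estimate?** The documents give no inputs, so this is an illustration with assumed values. Let *i* be the 10-month infection incidence among baseline seronegatives, *v* the share of them vaccinated during follow-up and *r* the antibody response. Then

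apparent sero-incidence = 1 − (1 − *i*)(1 − *v r*).

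- *i* = 0.05, *v* = 0.25, *r* = 0.7: 1 − 0.95 × 0.825 = 0.216.
- *i* = 0.05, *v* = 0.50, *r* = 0.9: 1 − 0.95 × 0.55 = 0.478.

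A true 5% would then appear as about 22% to 48%. This shows sensitivity and is not a forecast.

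**3. The plan's own sample size.** Inputs from section 2.5: a sample that "is required to estimate a proportion of 0.5 with a half-width of 5%, using a 95% Wilson score CI"; "15 participants (7 residents and 8 staff) per institution after 10 months of follow-up, and an ICC of 0.12"; drop-out 0.2 for staff and 0.4 for residents.

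- Wilson half-width at p = 0.5 is 1.96 / (2√(n + 3.84)). At n = 381 it is 0.04995, so 381 is right.
- Design effect 1 + 0.12 × 14 = 2.68; 381 × 2.68 = 1021.08, rounded up to 1022; 1022 / 15 gives 69 homes; 69 × 15 = 1035.
- Retention 10 × 0.8 + 12 × 0.6 = 15.2 per home; 22 / 0.5 = 44; 69 × 44 = 3036.

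Everything reproduces. Only the 50% premise is in question.

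**4. The same method with other seronegative shares.** Let *s* be the seronegative share at baseline. Per home at month 10, m = *s* × (20 × 0.8 + 24 × 0.6) = 30.4 *s*. Then N = 69 m, DE = 1 + 0.12 (m − 1) and n_eff = N / DE. The half-width is the Wilson one: z√(p(1 − p)/n + z²/(4n²)) / (1 + z²/n), with n = n_eff.

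| *s* (assumed) | Seronegative per home | m | N | DE | n_eff | Half-width, p = 0.5 (points) | Half-width, p = 0.1 (points) |
|---|---|---|---|---|---|---|---|
| 50% (plan) | 22.0 | 15.2 | 1049 | 2.70 | 388 | 4.95 | 3.0 |
| 20% | 8.8 | 6.08 | 420 | 1.61 | 261 | 6.0 | 3.7 |
| 15% | 6.6 | 4.56 | 315 | 1.43 | 220 | 6.5 | 4.0 |
| 10% | 4.4 | 3.04 | 210 | 1.24 | 169 | 7.5 | 4.6 |
| 5% | 2.2 | 1.52 | 105 | 1.06 | 99 | 9.7 | 6.0 |

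The loss is cushioned because smaller clusters lower the design effect.

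**The case against.** The objective says sero-incidence, not infection incidence, and section 1 makes follow-up of the vaccine-induced response one of the study's interests. Infection after vaccination has its own analyses with PCR, antigen, CT or saliva events. Vaccination is recorded for everyone, and an analysis plan that is not shown may carry the missing rule. The 50% was a planning input from late 2020; changing it now alters neither enrolment nor data.

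Part of this stands. No sentence says that every conversion counts; that is the effect of a missing event definition combined with the positivity rule. The documents also do not say which antigen the rapid test detects, although objective 7 relies on it to show vaccine response. The sample-size point is therefore one for reporting, not for recruitment.

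The rest does not remove the problem. What a primary outcome counts belongs in the protocol, and section 3 was amended after vaccination began without settling it. If vaccine response is of interest, that is a reason to report it separately. Objectives 5 and 8 do not supply an overall infection incidence.

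**Conclusion.** The point holds, as a cheap improvement. Followed as written, primary objective 2 gives a pooled estimate that cannot be read as infection incidence.

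Three stronger readings are tempting and are not supported:

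- *The estimate will mainly measure vaccine response.* The share cannot be determined from the documents. Participants already vaccinated and seropositive at baseline are not at risk of converting. The 22% to 48% above rests wholly on assumed inputs.
- *The at-risk set is far smaller than planned.* The 15% figure is for staff only and describes vaccination, not serostatus. Residents are 1656 of 3036, and neither their coverage nor the baseline seroprevalence is given.
- *The ±5-point precision is lost.* This is conditional. At p = 0.5 the half-width exceeds 5 points at each assumed share of 20% or less. At a true incidence of 10% it stays below 5 points down to 10% seronegative and reaches 6.0 only at 5%.

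The half-widths keep the plan's 69 homes, ICC of 0.12 and drop-out rates. The separate seroprevalence calculation (54 homes, 2376 participants) does not depend on the 50% premise beyond its use of 44 per home.

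**What to change.** Report objective 2 as two estimates.

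(a) Infection-related sero-incidence, in two analyses:

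- Rapid-test seroconversion among baseline seronegatives, with follow-up censored at first vaccination and those already vaccinated left out of this at-risk set. Since tests are two-monthly, follow-up in effect ends at the last test before the first dose. The questionnaires in appendix 6.3 already ask for that date.
- Anti-NCP seroconversion for all participants, on the dried blood spots that appendix 6.4 collects with every rapid test and plans to analyse by anti-S1/anti-NCP ELISA. State the assumption that the listed vaccines do not induce anti-NCP; the documents do not confirm it.

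Reported PCR or antigen positives should be supporting only, because section 1 says such testing under-ascertains infection.

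(b) Vaccine-related seroconversion, reported separately.

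In section 2.5, note that the 50% premise predates vaccination, and restate the expected half-width from the observed number of baseline seronegatives. Do not enlarge the sample.

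The cost is one amendment and some analysis wording, with no new sampling. The downsides are dependence on ELISA turnaround, possibly less favourable stated precision, and a smaller at-risk set for the censored analysis. With 15% of staff unvaccinated, that set holds on average about 0.15 × 20 = 3 staff per home before seropositives are removed.
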